### Ethical approval and registration

The study protocol was approved by the local ethics committee (Friedrich-Alexander-Universität Erlangen-Nürnberg (FAU), No. B18_20) and complied with the Declaration of Helsinki. Written informed consent is obtained from each subject and next-of-kin by the investigators before the subject enters the trial. The study is registered with clinicaltrials.gov (Identifier NCT04713085). If protocol modifications are required, amendments will be submitted to and approved by the local ethics committee. To disseminate our findings, the clinical trial results will be published in peer-reviewed journals. Additionally, the study’s protocol is in congruence with the SPIRIT 2013 statement [15]; the SPIRIT checklist has been added to this publication.

### Organizational aspects of the trial

The coordinating project management group evaluates the trial’s progress and publishes necessary reports. Communication between ethics committee, patient groups and members of the trial’s staff is provided by the principal investigator, being the head of the coordinating project management group (meetings 4 per year). The trial steering committee coordinates organizational matters and documentational aspects (meetings 1 per month). Performing medical investigators meet once a month and are providing day by day support and patient’s contact. If protocol modifications are required, sponsors and funders are notified first by the project management group. The participating center will be informed based on a revised protocol, which will be sent as soon as the principal investigator, sponsors and funders are in agreement. Changed amendments will furthermore be submitted to and approved by the local ethics committee and updates will be uploaded at clinicaltrials.gov. Any deviations from the protocol will be fully documented using a breach report form. There are no external auditing trials planned, as this is a low-risk intervention.

In case of technical problems of applied devices with consecutive recalls, the trial is terminated by the principal investigator and interim results might then not be published.

### Patient and public involvement

The study supports patient and public involvement to improve the study’s design and outcome variables. Based on suggestions from patients and patients’ organizations at the beginning of the trial, inclusion criteria, documentation of data and outcome variables were modified. Further suggestions are repeatedly evaluated in regular meetings of the study’s head and possibly implemented as modification (see above).

### Study outcomes

Participants are required to complete bowel movement diaries throughout the trial to the first target point. Children aged up to 7 years are thereby represented by their next-of-kin, whereas participants ≥ 13 years of age are advised to fill in the questionnaires by themselves. Between age 8 to 12, documentation is conducted together and depending on the child’s autonomy. At routine check-ups at baseline, 4 weeks, 3 and 6 and 12 months, specialized questionnaires must be completed. Quality of life analysis is conducted at baseline and after 3, 6 and 12 months, as described below (Fig. 4).

#### Primary outcomes and measurement

Primary outcome variables are defined, and change is measured between time points of baseline, 3 and 6 months of therapy as follows:Episodes of abdominal pain: Number of episodes of abdominal pain per weekDefinition of success: reduction by at least 50% of episodes per weekEpisodes of FI: Number of episodes of FI per weekDefinition of success: reduction by at least 50% of episodes per weekDefecation frequency: Number of bowel movements per weekDefinition of success: doubling of episodes per week to at least 3 or more bowel movements per weekStool consistency: Daily assessment of Bristol Stool Scale [16]Definition of success: change of at least 2 points within the scale of 1-7

Patients are classified based on treatment response and efficacy. A “clinically relevant” improvement is defined in cases with at least 2/4 fulfilled criteria, in which symptom control or -reduction is achieved.

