**Methods:**

A monocentric, randomized, unblinded, parallel-group trial is conducted. SNM is conducted in the invasive variant and in an innovative, external approach with adhesive electrodes (enteral neuromodulation, ENM). We include patients with constipation according to the ROME IV criteria and refractory to conventional options. Patients with functional constipation and Hirschsprung’s disease are able to participate. Participants are allocated in a 1:1 ratio to either SNM or ENM group. Clinical data and quality of life is evaluated in regular check-ups. Neuromodulation is applied continuously for 3 months (end point of the study) with follow-up-points at 6 and 12 months. Findings are analyzed statistically considering a 5% significance level (*p* ≤ 0.05). Outcome variables are defined as change in (1) episodes of abdominal pain, (2) episodes of FI, (3) defecation frequency, (4) stool consistency. Improvement of proprioception, influence on urinary incontinence, quality of life and safety of treatment are assessed as secondary outcome variables. We expect a relevant improvement in both study groups.

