## Materials and design

### Study objective and hypotheses

The aim of the study is to investigate the effects of SNM on symptoms and quality of life in children and adolescents. We intend to demonstrate that SNM is safe and effective in treatment of constipation and FI refractory to conventional therapeutic options.

The following hypotheses will be investigated within 3 months of treatment:(A)SNM is superior to ENM regarding treatment of abdominal pain as main symptom of refractory chronic constipation in childhood and adolescence.(B)Further exploratory hypotheses will be evaluated:SNM/ENM is effective and safe in reducing symptoms of chronic constipation and FI in children and adolescents as an additional therapeutic approach while continuing conventional treatment options unchanged.SNM/ENM treatment is effective in the subgroup of patients with Hirschsprung’s disease (HD).

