### Trial design

This is a monocentric, randomized, unblinded, 2-arm parallel-group trial in a 1:1 allocation ratio. The study is conducted at the University Hospital Erlangen, Friedrich-Alexander-Universität Erlangen-Nürnberg (FAU) from 2019 to 2023. Potential subjects are screened among patients attending pediatric surgical and pediatric gastroenterological clinics. Diagnoses are made according to the ROME IV criteria for FC [12]. Interventions are provided to subjects based on their group assignment of either 3 months of SNM or ENM therapy. Regular checkups and a follow up appointment are conducted within the trial and after 6 and 12 months after the initiation of the intervention. All participants are informed of the purpose of the study and obtain their informed consent before participating in this parallel group study. The subjects may choose to withdraw from the study, or they may be withdrawn from the study, at any time at the discretion of the investigator. If a subject withdraws or is withdrawn, every effort is made to complete and report the observations. The study design is presented in Fig. 3.

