#### Group 1: enteral neuromodulation

ENM is continuously applied for 12 weeks in each patient. Stimulation intensity is individually set by each patient to achieve a comfortable stimulation below pain threshold.

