#### Group 2: sacral neuromodulation

With the implantation of the electrode, stimulation of S3/4 is continuously applied. Patients are able to set stimulation intensity parameters within a preset range via an external device with or without the IPG.

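### The primary outcomes include a 6-month on-therapy time point, but the plan gives about 3 months of treatment and elsewhere treats month 6 as follow-up

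*Protocol article*

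**What the plan says.** Primary outcomes and measurement covers abdominal pain, fecal incontinence, defecation frequency and stool consistency, and states for all four that "change is measured between time points of baseline, 3 and 6 months of therapy as follows".

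The other statements on duration and timing are:

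- Abstract, Methods: "Neuromodulation is applied continuously for 3 months (end point of the study) with follow-up-points at 6 and 12 months".
- Study objective and hypotheses, before the superiority hypothesis on abdominal pain: "The following hypotheses will be investigated within 3 months of treatment".
- Trial design: "Interventions are provided to subjects based on their group assignment of either 3 months of SNM or ENM therapy". The later visits are set at "after 6 and 12 months after the initiation of the intervention".
- Group 1 (ENM): "ENM is continuously applied for 12 weeks in each patient".
- Group 2 (SNM): "With the implantation of the electrode, stimulation of S3/4 is continuously applied". No end of stimulation is given there. The Technique section describes a pulse generator implanted subcutaneously 4 weeks after the electrode and does not mention switch-off or removal.

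On measurement, Study outcomes asks participants to "complete bowel movement diaries throughout the trial to the first target point", a point that is not defined. The same section schedules questionnaires at baseline, 4 weeks, and 3, 6 and 12 months.

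**The concern.** The definition of the primary outcomes assumes a treatment period that the rest of the plan does not provide. If it is followed as written, one of the two primary comparisons is made after planned ENM has ended, while the superiority hypothesis concerns the first 3 months. Nothing in the outcome definition says whether month 3 or month 6 decides, so the answer could be settled after both results are seen.

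The trial compares an operation with adhesive electrodes in children, so the contrast behind the main claim should be clear. A month-6 difference could arise from a difference between the techniques, from one arm still being stimulated, or from differing persistence of effect after stimulation stops. The plan does not allow these to be told apart.

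**Working it through.** **1. Timing.** ENM lasts 12 weeks, which is 84 days or about 2.8 months. The 6-month visit is counted from the start of the intervention, so it falls at about week 26. 26 − 12 = 14 weeks after planned ENM ends. As planned, no ENM patient has 6 months of therapy at that visit.

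**2. Status of month 6.** It is a primary time point in the outcome definition and a follow-up point in the abstract. The hypotheses are limited to 3 months. The sample size section bases power on abdominal pain and gives no time point, so it does not settle the matter.

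**3. SNM at month 6.** Trial design gives 3 months for both arms. The Technique and Group 2 sections describe an implanted generator and continuous stimulation with no stated end. The two readings are therefore both arms off, or SNM on and ENM off. If the outcome definition is itself right about duration, a third is both arms on. The text does not choose between them.

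**4. Instrument at month 6.** The end of the diary period is undefined. Given the 3-month end point in the abstract, month 3 is the natural reading. If so, the diary has ended by month 6, and the stool score, which is defined as a daily assessment, has no evident source there. For the other three outcomes, the questionnaires are scheduled at baseline and at month 6 and include current defecation status, so one instrument could serve at both times.

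**5. Illustration of size.** The plan's 39 per group is not in dispute. Its base rates are not stated; 50% versus 80%, two-sided and without continuity correction, gives exactly 39 per arm with 80.5% power. The illustration takes n = 39 per arm and two-sided α = 0.05 (sidedness is not stated in the article). It assumes equal techniques with 70% response, SNM left on at 70%, and ENM losing a share of its responders after week 12. With p̄ the mean of the two rates:

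z = [ |p₁ − p₂| − 1.96·√(2p̄(1 − p̄)/n) ] / √( (p₁(1 − p₁) + p₂(1 − p₂))/n ), and the chance of significance is Φ(z).

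| ENM responders lost | SNM vs ENM at month 6 | z | Chance of p ≤ 0.05 |
|---|---|---|---|
| one tenth | 70% vs 63% | (0.07 − 1.96×0.1069)/0.1066 = −1.31 | 10% |
| one fifth | 70% vs 56% | (0.14 − 1.96×0.1093)/0.1082 = −0.69 | 25% |
| one third | 70% vs 47% | (0.23 − 1.96×0.1116)/0.1085 = 0.10 | 54% |
| one half | 70% vs 35% | (0.35 − 1.96×0.1131)/0.1059 = 1.21 | 89% |

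By exact enumeration with Fisher's test, one of the two tests the article names, the last three rows become 18%, 46% and 84%. With the chi-square test they are 25%, 55% and 89%.

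**The case against.** A reader might infer that month 6 compares active SNM with stopped ENM. The document does not say so. Trial design states 3 months for both arms, and the abstract makes no distinction between them. A condensed article may leave the handling of the device after month 3 to the full protocol, so silence about switch-off is weak evidence. If both arms stop at 3 months, the illustration in the table does not apply. This stands: unequal stimulation is possible, not established.

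A reader might also infer that the instrument changes from diary to recall between baseline and month 6. No passage says baseline is taken from the diary, the questionnaires are scheduled at both times, and the schedule figures are not visible here. This stands too. Only the daily stool score lacks an evident source at month 6, and that depends on how the undefined end of the diary period is read.

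The assumed response and relapse rates have no source in the document. The only ENM response figure it gives is 86%, from the earlier ENM trial described in the Discussion. The percentages in the table therefore cannot be read as the trial's error rate.

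Finally, the abstract and the hypotheses both point to month 3. The statistical section promises p-value adjustment for multiple analyses, and the Discussion calls all p-values explorative. A month-3 test of the superiority hypothesis is untouched by any of this. These points lower the stakes, but the outcome definition still lists month 6 as primary, in conflict with the abstract.

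**Conclusion.** The contradiction in the current text is certain: the primary outcomes are defined at 6 months of therapy, while the abstract, Trial design and the ENM arm description plan 3 months or 12 weeks. A month-6 primary comparison would be made about 14 weeks after planned ENM ends, would not test the 3-month hypothesis, and leaves unclear which time point decides.

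Unequal stimulation at month 6 and a change of instrument remain possibilities. If SNM stayed on and ENM responders relapsed, equal techniques could look different. The illustrative chance of significance, about 10% to 89%, depends entirely on the assumed 70% response and on a loss of between one tenth and one half of ENM responders.

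This should be fixed. It does not invalidate the trial, because the month-3 comparison is unaffected once it is named as the sole primary one.

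**What to change.** Before analysis:

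- Name month 3 as the only primary time point, in line with the abstract and the hypotheses.
- Label month 6, like month 12, as follow-up and report it descriptively.
- Report stimulation status (on, off or removed) by arm at month 6.
- State which instrument supplies each outcome at each visit, define the end of the diary period, and say what supplies the stool score at month 6.

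The investigators must also reconcile the treatment-duration statements in the abstract, Trial design, the two arm descriptions and the primary outcome definition. No view is taken here on which duration is right.

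The cost is a change of wording plus a tabulation of stimulation status, which may have to be drawn from existing records. A repeat diary before the month-6 visit is probably no longer possible, because data collection was due to finish in December 2023 and the article appeared in March 2024.

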### Study population: eligibility criteria

#### Inclusion criteria

To be eligible for participation, subjects are required to fulfill the following criteria:age between 2–17 yearsinformed consentchronic constipation according to the ROME IV criteria for more than 3 months with abdominal pain and with or without FI [12] despite underlying diseases such as FC, rectal evacuation disorders or HD.refractory to conventional treatment in an appropriate weight-adapted application (training for bowel movements, lifestyle changes, pelvic floor training, pharmacological options)in cases of HD: diagnosis confirmed histologically by rectal biopsies and in case of resection of an aganglionic segment: period between surgery and SNM at least 1 yearin cases of anorectal malformation or mechanical obstruction: post-surgical status: period between surgery and SNM at least 1 year

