#### Sample size calculation

As there is still insufficient clinical evidence on neuromodulation treatment in children and adolescents with FC and HD, this study requires only a small sample size. Power analysis is based on abdominal pain as primary outcome variable. A minimum of 78 subjects in total and 39 subjects per group is powered to detect a difference of at least 30%, with a 95% confidence interval (α = 0.05) and statistical power of 80% (β = 0.2).

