#### Secondary outcomes and measurement

Secondary outcome variables are defined as follows:Improvement of proprioception: as mentioned in the specialized questionnairesEpisodes of urinary incontinence: the number of episodes per week is evaluated with the criterion for a clinically relevant improvement in cases of reduction by at least 50% of episodes per week.Quality of life: assessment based on the KINDL^R^ questionnairesSafety of treatment: adverse events as mentioned in the specialized questionnaires

FI is diagnosed at the age of ≥ 4 years in cases of prior adequate toilet training and urinary incontinence at the age of ≥ 6 years with at least 4 episodes per week.

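### The stool-consistency and FI success rules, and the 2-of-4 composite built on them, misclassify patients if applied as written; the abdominal pain comparison is unaffected

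*Protocol article*

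**What the plan says.** All references are to the protocol article.

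- **Primary outcomes and measurement** lists four primary outcomes, each with a success definition. Abdominal pain and FI need weekly episodes to fall by half or more. Defecation frequency needs a doubling that reaches three or more per week. Stool consistency needs a "change of at least 2 points within the scale of 1-7". The first three have a direction; the stool rule has none.
- The same section defines the composite: clinically relevant "improvement is defined in cases with at least 2/4 fulfilled criteria, in which symptom control or -reduction is achieved". The denominator is four for every patient.
- **Inclusion criteria** admit children aged 2 to 17 with chronic constipation "with abdominal pain and with or without FI". Pain is required at entry; FI is not.
- **Secondary outcomes and measurement** adds that "FI is diagnosed at the age of ≥ 4 years in cases of prior adequate toilet training".
- **Sample size calculation**: "Power analysis is based on abdominal pain as primary outcome variable".
- **Statistical analysis** compares clinical outcomes with chi-square and Fisher's exact tests, so the success classifications are what gets tested.

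**The concern.** The stool rule, taken at its word, accepts movement either way along the scale. In a constipation trial, harder stool would then score the same as the intended softening, and so would overshooting into very loose stool.

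The FI rule has a different fault. A child with no episodes at baseline has nothing to halve. One analyst could code success (zero is no more than half of zero) and another failure (no reduction occurred). Children aged 2 or 3 add a further ambiguity: FI is not diagnosed at that age, and the article does not say whether their episodes count.

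Both faults pass into the composite. At stake are the response rates for stool consistency, FI and clinically relevant improvement, and with them the exploratory claims under hypothesis B that SNM and ENM are effective. Direction-free scoring and a favourable zero-baseline coding would both raise those rates. In a trial with unblinded patients and patient-reported outcomes, the coding should not be left open until the data are in hand.

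**Working it through.** **The plan's own figure.** The only related number is 39 per group. With a two-sided pooled test, alpha 0.05, power 80% and assumed rates of 50% and 80%:

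n = [1.96 × √(2 × 0.65 × 0.35) + 0.8416 × √(0.25 + 0.16)]² / 0.30² = (1.322 + 0.539)² / 0.09 = 38.5, so 39.

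The article gives no base rate. Other base rates with a 30-point difference give 27 to 43 without continuity correction. The figure is plausible but cannot be confirmed. It concerns abdominal pain, and nothing below depends on it.

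**Step 1: stool rule, by enumeration.** On a 1 to 7 scale, the ordered pairs that differ by 2 or more number 5 + 4 + 3 + 2 + 1 = 15 in each direction, 30 in all. A child starting at 3 passes by ending at 1, 5, 6 or 7; a child starting at 4 passes by ending at 1, 2, 6 or 7. If the target zone were types 3 to 4 (assumed), 13 of the 30 pairs end further from it than they began; with types 3 to 5, 12 do. These are counts of pairs, not probabilities.

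**Step 2: stool rule, chance passes.** Assume change is normal with mean 0 and standard deviation SD. The article gives no SD, so 1.5 is assumed, with a range of 1 to 2.

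| SD | Either direction: 2 × [1 − Φ(2/SD)] | One direction: 1 − Φ(2/SD) |
|---|---|---|
| 1 | 5% | 2% |
| 1.5 | 18% | 9% |
| 2 | 32% | 16% |

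**Step 3: composite by FI status.** Assume independent criteria, each met with probability q.

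- Child with FI, 2 of 4 needed: 1 − (1−q)⁴ − 4q(1−q)³
- Child without FI, FI coded as failure, 2 of 3 needed: 3q²(1−q) + q³
- Child without FI, FI coded as success, 1 of 3 needed: 1 − (1−q)³

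At q = 0.4:

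- with FI: 1 − 0.1296 − 0.3456 = 0.525
- without FI, coded as failure: 0.288 + 0.064 = 0.352
- without FI, coded as success: 1 − 0.216 = 0.784

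| q | With FI | No FI, coded failure | No FI, coded success |
|---|---|---|---|
| 0.2 | 18.1% | 10.4% | 48.8% |
| 0.3 | 34.8% | 21.6% | 65.7% |
| 0.4 | 52.5% | 35.2% | 78.4% |
| 0.5 | 68.8% | 50.0% | 87.5% |

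**Step 4: overall rate.** The share without FI is not given. If it is half and q = 0.4, the composite rate is 0.5 × 0.525 + 0.5 × 0.352 = 43.8% under one coding and 0.5 × 0.525 + 0.5 × 0.784 = 65.4% under the other. The difference of about 22 points comes from an unstated choice.

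**Step 5: does a chance imbalance in FI matter between arms?** With 39 per arm and half the children having FI, the SD of the between-arm difference in FI share is √(2 × 0.25 / 39) = 0.113. At q = 0.4 with FI coded as failure, the gap between children with and without FI is 0.525 − 0.352 = 0.173. The arm difference then moves by 0.113 × 0.173 = 2.0 points at one SD and 3.8 points at 1.96 SD. That is small beside the planned 30% difference.

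**The case against.** **The main comparison is not touched.** This stands. Hypothesis A and the power calculation rest on abdominal pain, which every child must have at entry and which has a directional rule. The other hypotheses are labelled exploratory. A reader might infer that the primary outcomes as a whole, or N = 78, are compromised; the article does not support that.

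**The article plainly means improvement.** This stands as to intent. The rule is labelled as success, and the composite sentence speaks of symptom control or reduction. A reader might infer that the trial sets out to score harm as benefit; that is not supported. But the qualifying clause belongs to the composite and gives the stool criterion neither a direction nor a target.

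**The stool percentages are soft.** This also stands. The SD is assumed, the normal model ignores the ends of the scale, and a child starting at 1 or 2 cannot fall by 2 points. The harder-stool error is open only to children starting at 3 or above. The figures are illustrations.

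**Zero-baseline coding belongs in the SAP, and the age rule implies that only diagnosed FI counts.** This stands only in part. The age rule hints at an evaluable group but does not restrict the outcome to it, and the composite keeps a denominator of four for all. The difficulty lies in rules that the article states, not in detail it leaves out.

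**Two further inferences do not hold.** A reader might think that a chance imbalance in baseline FI materially distorts the comparison of arms; Step 5 shows a shift of about 2 to 4 points. A reader might also fault the defecation rule because a child already at three per week must reach six. That is demanding, but clear and directional, and is not part of this point.

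**Conclusion.** The concern holds within limits. Stool consistency, FI and the 2-of-4 composite have success rules that misclassify patients if followed literally. Abdominal pain is sound, and so are hypothesis A and the sample size as far as this point goes.

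That the stool rule lacks a direction and that FI cannot be halved from zero follow from the text and need no assumption. The sizes do need assumptions. The stool figures (18% against 9% at SD 1.5) rest on no mean change, an unsourced SD and an unbounded normal model. The composite figures (35% or 78% for a child without FI, against 52% with FI) rest on independent criteria with a common success probability of 0.4. Correlated criteria would change them. The true share of children without FI is not in the article, so the actual misclassification cannot be computed from it.

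**What to change.** 1. **Stool consistency.** Define success as a shift of at least 2 points toward a target range that the investigators name in advance. Count shifts away from that range as failure, and state how overshooting, and a child already in the range at baseline, are scored.
2. **FI.** Analyse the success criterion only in children with FI at baseline, and say how children below the diagnostic age are treated.
3. **Composite.** State in advance how a non-applicable FI criterion counts, for example that FI is never counted as met at a zero baseline. Report the composite stratified by baseline FI, because under that rule a child without FI must still meet 2 of 3 rather than 2 of 4.

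**Cost.** This means rewording and recoding data already collected. Response rates may be somewhat lower. Fewer children are evaluable for FI: if 30 to 70% have none at baseline (assumed), about 27 to 12 per arm remain, with power of about 60% to 30% for 35% against 65%, compared with 77% at 39 per arm. The article puts the end of data collection at December 2023, so the change alters outcome definitions at or near the end of an open-label trial. It should be fixed, dated and documented as an amendment before the analysis.
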